### Aim 2 Overview: Design and “Build” a Treatment Manual

#### Overview

The goal of Aim 2 is to design and build (ie, write) a treatment manual to treat the lasting and varied multidimensional impact of PMIEs. The treatment manual will be written based on Aim 1 findings, clinical evidence and theory, and feedback from the clinical expert panel. User-centered design suggests that, in the design phase, important tasks involve synthesizing user needs, developing a low-fidelity prototype, and gathering usability data from potential users (eg, providers who may use the manual).

The PI will lead treatment manual writing in close consultation with coinvestigators, consultants, and the clinical expert panel. The manual will be iteratively revised based on data gathered from Aim 1 interviews, the clinical expert panel, and once the pilot trial commences, feedback from pilot trial participants.

#### Clinical Expert Panel Feedback on the Treatment Manual

A panel of expert clinicians will convene to provide guidance on the development of the treatment manual, including reviewing and providing constructive criticism on iterative drafts of the manual. The clinical expert panel will provide a perspective on the usability and learnability of the manual for nonrelational dynamic future users, in particular. The clinical expert panel may also suggest new approaches, which will be discussed with the study team. Importantly, the clinical expert panel will not receive any sensitive or identifiable data.

#### Qualitative Data Analysis Plan

Clinical expert panel meetings will be conducted and data analyzed using the RQA for qualitative data [44].

#### Reinterview VA Trauma Clinicians to Gather Feedback on the Treatment Manual (n=~20)

We will recontact the clinicians who participated in the Aim 1 interview to obtain their feedback on drafts of the treatment manual. Interviews with VA trauma clinicians will occur via teleconference. Interviews will be conducted, and data will be analyzed using RQA for qualitative data [44]. We will use the think-aloud strategy to guide semistructured interviews. The think-aloud method involves potential users reviewing the treatment manual while simultaneously and continuously speaking about their reactions, which the researchers record. The think-aloud method is recommended by user-centered design experts for the design phase.

### Aim 3 Overview: Test the Treatment Manual via 2 Open Pilot Trials

#### Overview

The goal of Aim 3 is to test the treatment manual via 2 iterative open pilot trials with PMIE-impacted veterans. User-centered design principles suggest that an intervention should be rapidly prototyped, piloted, and revised based on user feedback [25,45]. To achieve this aim, we will run two pilot trials of the PMIE-focused treatment manual in the CTVHCS mental health clinic. Data on usability, learnability, feasibility, and acceptability will be gathered from veterans and interventionists, and initial data on clinically meaningful outcomes will be gathered from veterans. The treatment manual will be revised at the end of the first pilot trial and will be finalized at the end of the second pilot trial.

#### Participants

We aim to enroll approximately 12 PMIE-impacted US combat veterans total into 2 open pilot trials; approximately 6 veterans will be enrolled in each pilot trial.

#### Study Site

The pilot trials will be conducted in the CTVHCS mental health clinics. The mental health clinic is staffed by multidisciplinary care teams that provide comprehensive mental and behavioral health treatments, including psychosocial rehabilitation, substance use treatment, trauma-focused treatment, and chronic pain and physical disability-related treatments, as well as general mental health treatment.

#### Recruitment, Pre-Eligibility Screening, Consent, and Eligibility Screening

We will use the same methods for recruitment, pre-eligibility screening, consent, eligibility screening, and compensation, as used in Aim 1 interviews with PMIE-impacted veterans. See description of Aim 1 methods for details. See Table 4 for eligibility screening measures.

#### Inclusion/Exclusion Criteria

We will use the same inclusion and exclusion criteria for the pilot trials as used in Aim 1 interviews with PMIE-impacted veterans. This will increase the likelihood that user-centered recommendations will fit the intended treatment sample.

#### Sample Size Justification

We aim for 6 to 8 participants per group based on recommendations for group therapy sizes; we will recruit up to ten participants per group to account for expected dropout [22].

#### Treatment Delivery and Supervision

The PMIE treatment manual designed in Aim 2 will be delivered to 2 successive open pilot groups. Based on the PI’s experience providing nonmanualized PMIE-focused group psychotherapy and clinical literature that suggests more sessions are needed or complex psychological problems [46], we expect the group to be approximately 25 weekly sessions. Each session will be 90 minutes each. The group will be led by 2 trained mental health providers. Procedures for identifying and handling treatment dropouts (eg, how many missed sessions until a participant is considered “dropped out”) will be developed as part of this pilot trial. Participants that cease attending treatment sessions will be recontacted to complete follow-up assessments. Interventionists will receive ongoing supervision via regularly scheduled teleconferences.

#### Risk Assessment Plan

Participants will receive 3 follow-up check-in phone calls following the end of the treatments: the first at one-month posttreatment, the second at 3-month posttreatment, and the third at 6-month posttreatment. During these follow-up phone calls, participants’ suicide risk will be assessed using the C-SSRS. We will follow the CTVHCS Memorandum 116A-005 (the latest version), “Suicide Prevention and Management of Suicidal Behavior,” to guide risk assessment and treatment planning. All participants, regardless of response on the C-SSRS, will be offered referrals to mental health services as requested or needed.

#### Study Measures and Participant Characterization

See Table 4 for study measures, assessment time points, and participant pay. Most study measures are self-report and will be completed via VA REDcap (Research Electronic Data Capture; Vanderbilt University) survey. Participants will be characterized based on demographic and medical history data, including data collected via the VA electronic health record: age; ethnicity; psychiatric treatment history, including recent psychiatric admission; medications and medical history; years of education; marital status; housing; disability and employment status; history of childhood trauma; and past and current mental health diagnoses in the electronic health record problem list.

Participants will complete study measures at 3 time points: a baseline assessment prior to group psychotherapy, following the end of the group therapy (approximately 6 months postbaseline), and 6 months after the end of the group psychotherapy (approximately 12 months postbaseline). Participants will also be called approximately 3 months after the end of group psychotherapy for a clinical check-in; at this time point, only the C-SSRS will be administered. Participants will be contacted via IRB-approved methods up to 3 times to complete each assessment.

#### Primary Outcome Measures: Feasibility and Acceptability

Acceptability and feasibility will be assessed in several ways: (1) actual recruitment versus planned recruitment; (2) participants’ number of sessions completed and number of dropouts; (3) qualitative interview data from interventionists, collected by the PI during weekly supervision sessions, regarding reactions to the treatment manual and satisfaction with the treatment manual; and (4) qualitative interview data from veterans on participants’ enthusiasm for the therapy, comprehension of therapy, and application of therapy interventions, collected by the PI or approved study team member during follow-up exploratory outcome assessment phone calls. Veterans and providers will also complete three 4-item measures that were developed by the user-centered design methodologists: Acceptability of Implementation Measure (AIM), Implementation Appropriateness Measure (IAM), and the Feasibility of Intervention Measure (FIM) [47]. The AIM, IAM, and FIM scores demonstrated adequate reliability and validity in initial psychometric testing in samples of mental health professionals. Usability and learnability will be assessed via the Intervention Usability Scale (IUS) and qualitatively gathered feedback from SO and GB. The 10-item IUS was adapted from the widely used System Usability Scale. It is scored on a Likert-style scale ranging from 0 (strongly disagree) to 4 (strongly agree) and provides a percentile ranking of usability.

#### Exploratory Clinical Outcomes

The primary exploratory outcome is functional impairment, assessed using the SDS [39]. We will also collect exploratory data on secondary outcomes. PTSD will be measured with the widely used 20-item Posttraumatic Stress Disorder Checklist for *DSM-5* (*Diagnostic and Statistical Manual of Mental Disorders* [Fifth Edition]; PCL-5), which assesses severity of each *DSM-5* PTSD symptom using a Likert-style scale ranging from 0 (not at all) to 4 (extremely) [48]. A total score of 31‐33 is suggestive of a PTSD diagnosis. The PCL-5 demonstrated Cronbach α=0.95 in a sample of veterans in the VA [49]. Depression will be measured with the 21-item Beck Depression Inventory-II (BDI-II), which uses a Likert-style scale ranging from 0 to 3 [50]. The BDI-II is widely used, with Cronbach α=0.92 in samples of adults. Suicidal ideation will be measured using the Beck Scale for Suicide Ideation (BSS), which is extensively used in treatment studies of suicidal individuals [51]. The BSS is rated on a Likert-style scale ranging from 0 to 3, and scores have Cronbach α>0.90 in both inpatient and outpatient settings. Spiritual distress will be measured with the 26-item Religious and Spiritual Struggles Scale (RSSS), which assesses 6 domains, including moral and doubt struggles, using a Likert-style scale ranging from 0 to 5 [52]. We will also collect data on group cohesion to examine group-specific contributions to outcomes using the 25-item Group Cohesion Scale-Revised [53], which measures group functioning on a Likert-style scale ranging from 0 (low) to 4.

We will also collect exploratory data on moral injury-specific outcomes using the MIOS [38], the 9-item Moral Injury Events Scale (MIES) [54], the 20-item Moral Injury Questionnaire–Military version (MIQM) [55], and the 17-item Expressions of Moral Injury Scale (EMIS) [56]. Data on the MIOS, MIES, MIQM, and EMIS will also allow results from this study to cross-talk with external efforts to map and treat the impact of moral injury, such as the VA-funded ACT for Moral Injury trial (RX002854-01A1).

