Clinical expert panel reviews treatment manual												✓								
Treatment manual revision												✓	✓							
Second open pilot														✓	✓	✓	✓			
Recruitment, screening, and consent (n=6)														✓						
Treatment and supervision (2 interventionists)															✓	✓				
Data collection, analysis, and interpretation															✓	✓	✓		✓	
Revision of treatment manual																	✓	✓	✓	✓
Develop a fidelity and competency scale																	✓	✓		
Clinical expert panel reviews manual and new scale																		✓		

a PMIE: potentially morally injurious event.

b VA: Department of Veterans Affairs.

c PI: principal investigator

**Table 3. T3:** Summary of data collection and analysis.

User-centered design phase, participants, and role		Method and timing of assessment	Variables and topics	Analysis plan	Study aim
Qualitative data					
Discover					
Veterans: potential future users		One-time, one hour semistructured interview	Needs Preferences (eg, group vs individual) Barriers and facilitators to participation	Rapid qualitative analysis	Aim 1
Clinicians and potential future users		—^a^	Needs Preferences	—	Aim 1
Veterans: former users		—	Experiences Preferences Areas for improvement	—	Aim 1
Design and build					
Clinical expert review panel		Biannual semistructured focus group, in Years 1‐3	Techniques Goals Format Active ingredients		Aim 2
Clinicians and potential future users		Think aloud review of treatment manual, via one-time one-hour semistructured interview	Usability issues Future context		Aim 2
Test					
Veterans and pilot trial participants		One-time, one-hour semistructured interview	Acceptability Usability		Aim 3
Clinicians and Interventionists		Feedback during supervision	Usability Learnability Acceptability		
Quantitative data					
Veterans and pilot trial participants		Planned versus actual recruitment Number of completed sessions Number of dropouts Self-report measures completed 1-month and 6-month posttreatment Clinical measure	Pilot trial primary outcomes: Usability Feasibility Acceptability Pilot trial exploratory clinical outcomes	Descriptive statistics: Mean SD 95% CIs Standardized mean change, for exploratory clinical outcomes	Aim 3

a Not applicable.

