#### Consent, Eligibility Screening, and Compensation

If veterans pass prescreening criteria, they will be scheduled for an informed consent and eligibility screening appointment. The potential participant will complete the informed consent prior to completing eligibility measures due to the sensitive content of these measures. To assess eligibility, participants will complete the event screener and brief Inventory of Psychosocial Functioning (b-IPF) [37] from the Moral Injury Outcome Scale (MIOS) [38], the Sheehan Disability Scale (SDS) [39], the Columbia-Suicide Severity Rating Scale (C-SSRS) [40], and the Montreal Cognitive Assessment (MoCA) [41]. See Table 4 for study measures. They will also be asked about their alcohol and substance use and dependence. The informed consent and eligibility screening will take approximately 45‐60 minutes. If participants provide consent and are eligible, then they will complete the full MIOS measure; if veterans are not eligible, we will not administer these items to reduce participant burden. At the end of the informed consent and eligibility screening, veterans will be scheduled for a one-hour interview with members of the study team. Veterans will be compensated US $30 after completing this one-hour interview. Veterans who decline to participate in the study but report an interest in mental health treatment will receive appropriate referrals.

**Table 4. T4:** Table of veteran participant study measures.

Measurement information		Study aim 1: samples		Study aim 3			
Purpose and measure	Construct	Sample 1^a^	Sample 3^b^	Time points	Baseline	1month PG^c^	6 months PG
Eligibility (Aim 1, sample 1 and 3); descriptive (Aim 1, Sample 3)							
MIOS^d^ event screener	PMIE^e^ exposure	✓		✓		✓	✓
Eligibility, descriptive (Aim 1), exploratory outcome (Aim 3)							
SDS^f^	Functional impairment	✓		✓		✓	✓
b-IPF^g^, in MIOS	Psychosocial functioning	✓	✓	✓		✓	✓
Eligibility and safety							
C-SSRS^h^	Suicide risk	✓	✓	✓	✓	✓	
Eligibility							
MoCA^i^	Cognitive impairment	✓		✓			
Primary outcome (Aim 3)							
AIM^j^	Acceptability					✓	✓
IAM^k^	Implementability					✓	✓
FIM^l^	Feasibility					✓	✓
Descriptive (Aim 1); exploratory outcome (Aim 3)							
MIOS Outcome	Moral injury	✓	✓		✓	✓	✓
Exploratory outcome (Aim 3)							
PCL-5^m^	PTSD^n^				✓	✓	✓
BDI-II^o^	Depression				✓	✓	✓
BSS^p^	Suicidal ideation				✓	✓	✓
RSSS^q^	Spiritual distress				✓	✓	✓
MIES^r^	PMIEs				✓	✓	✓
MIQM^s^	Moral injury				✓	✓	✓
EMIS^t^	Moral injury				✓	✓	✓

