#### Inclusion and Exclusion Criteria

Inclusion criteria are male and female, English-speaking veterans, aged 18 years or older, enrolled in CTVHCS, with a service history of combat deployments or combat hazard pay. Participants must (1) comprehend and sign the informed consent form; (2) report a history of PMIEs, identified by the event screener of the MIOS; and (3) report functional impairment secondary to their PMIE, as identified by ≥3 on the MIOS functional impairment items and ≥10 on the SDS. We believe that it is best to let exposure to life-span fear-based traumatic events freely vary among our participants. The concern is that excluding danger-based exposures in war veterans will unduly bias our study group. The MIOS event screen asks participants to endorse their worst and most currently distressing PMIE, which increases the likelihood that participants’ reports of moral injury will be based on an event that currently haunts and consumes them. Because we are looking for a range of PMIE-related impact, participants are not otherwise included or excluded for interviews based on psychiatric diagnoses. Exclusion criteria are substance abuse or dependence (other than caffeine or tobacco dependence); prospective participants who have maintained sobriety for at least 6 weeks prior to the time of enrollment may be eligible. Veterans will be excluded if they are deemed to be at high risk of suicide; veterans who are deemed at low or medium risk of suicide are considered eligible for the study. Suicide risk is evaluated using the C-SSRS using procedures outlined in the Risk Assessment Plan (see below). The C-SSRS is the VA-mandated suicide screening tool used in primary care and mental health clinics across the VA. If immediate clinical attention is warranted, veterans will be provided care consistent with procedures outlined in the Risk Assessment Plan. Veterans may also be excluded if they report evidence of cognitive impairment as identified by MoCA scores ≤17.

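### Table 4 schedules no Baseline SDS, so if it is followed the lead exploratory clinical outcome is measured from the score used for selection, and its uncontrolled change is biased towards improvement

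*Protocol article*

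**What the plan says.** Under Exploratory Clinical Outcomes, the protocol article names the lead clinical measure: "The primary exploratory outcome is functional impairment, assessed using the SDS".

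The Inclusion and Exclusion Criteria for the Aim 1 veteran interviews require functional impairment "as identified by ≥3 on the MIOS functional impairment items and ≥10 on the SDS". The Aim 3 section carries this over: "We will use the same inclusion and exclusion criteria for the pilot trials as used in Aim 1 interviews with PMIE-impacted veterans". The SDS is therefore both an entry filter and an outcome in the pilot trials.

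Table 4 ticks the SDS and the b-IPF in the first Aim 3 column and at 1 and 6 months postgroup, with the Baseline cell blank. The MIOS event screener has the same pattern. The PCL-5, BDI-II, BSS, RSSS, MIES, MIQM, EMIS and MIOS outcome all have a Baseline tick.

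Study Measures and Participant Characterization says that study measures are completed at three time points, the first being a baseline assessment before the group starts. It makes no exception for the SDS, but it sends the reader to Table 4 for the time points.

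Table 3 gives the analysis as "Standardized mean change, for exploratory clinical outcomes" and does not name the standardiser. The Discussion acknowledges that there is no comparator group.

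**The concern.** If participants are admitted because a score is at or above a cut-off, and that same score is then the starting point for change, the group mean is expected to fall at the next measurement even if nothing has happened. Some people are admitted on an unusually bad day. Those with an unusually good day are turned away. Scores below 10 are impossible at the start and possible afterwards. Without a comparator, this fall cannot be separated from a treatment effect.

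The cut-off also narrows the spread of the starting scores. If change is divided by that narrowed SD, the standardised figure grows for a second, separate reason.

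What is at stake is an estimate, not a test. The article rejects formal hypothesis testing for these outcomes. The risk is that an SDS change that partly reflects selection is read as a signal on functional impairment, or is borrowed as an effect size for the later randomised trial.

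**Working it through.** **What the first Aim 3 column means.** It is headed only as time points. The MoCA, which serves only eligibility, has its single Aim 3 tick there, so the column is taken to be screening. On that reading, the SDS is scheduled before treatment only at screening.

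**Inputs.** From the article: cut-off 10, no comparator, about 12 participants. There is no SDS mean, SD, retest correlation or expected change to reproduce. The following are assumptions: normal scores; SD 7 among those screened; mean μ of 12, 14 or 18; correlation r between screening and follow-up, in the absence of any treatment effect, of 0.5 to 0.8, with 0.7 as the central value.

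**Formulae.** Let a = (10 − μ)/SD and λ = φ(a)/(1 − Φ(a)).
- Spurious fall with no treatment effect = (1 − r) × SD × λ.
- SD of the admitted screening scores = SD × √(1 + aλ − λ²).

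**Worked case, μ = 12.** a = −2/7 = −0.286 and λ = 0.3830/0.6125 = 0.625, so SD × λ = 4.38. The admitted mean is 12 + 4.38 = 16.38. At r = 0.7 the fall is 0.3 × 4.38 = 1.31 points. The admitted SD is 7 × √0.430 = 4.59.

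| Assumed μ | λ | Fall, r = 0.8 | Fall, r = 0.7 | Fall, r = 0.5 | Admitted SD |
|---|---|---|---|---|---|
| 12 | 0.625 | 0.88 | 1.31 | 2.19 | 4.59 |
| 14 | 0.473 | 0.66 | 0.99 | 1.66 | 4.98 |
| 18 | 0.238 | 0.33 | 0.50 | 0.83 | 5.74 |

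A simulation with whole-number scores held to an assumed range of 0 to 30 gave slightly smaller falls at r = 0.7: 0.91 at mean 14 and 0.46 at mean 18.

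**Standardised form.** At r = 0.7, the spurious fall divided by the admitted SD is 1.31/4.59 = 0.29 at μ = 12 and 0.50/5.74 = 0.09 at μ = 18. Truncation alone multiplies any genuine change standardised this way by 7/4.59 = 1.52 or 7/5.74 = 1.22. If the SD of change is used instead, truncation shrinks it only to 0.96 (μ = 12) or 0.98 (μ = 18) of its unrestricted value. The spurious fall itself remains under either standardiser.

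**Against the precision available.** With n = 12 and r = 0.7, the 95% CI half-width for mean change is about 2.201 × √(2 × 0.3/12) = 0.49 SD, or 0.492 × 7 = 3.4 points. A fall of 0.5 to 1.3 points is roughly 15% to 38% of that.

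**Effect of a separate Baseline.** In the simulation, change measured from a second, post-screening SDS showed a spurious fall between −0.02 and 0.01 points. The SD at that second measurement was 6.02, against 4.97 at screening (mean 14, r = 0.7). This assumes that day-to-day fluctuations at screening and Baseline are independent.

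**The case against.** The strongest reply is that a Baseline SDS may well be taken. The study-measures section speaks of a baseline assessment without exempting the SDS, and Table 4 is not beyond doubt. Its first Aim 3 column is identified only by inference from the MoCA row. It also gives the C-SSRS no 6-month tick, although the Aim 3 Risk Assessment Plan assesses it then. This stands in part. A reader might infer that the trial certainly has no baseline SDS, but the article does not establish that. It shows a schedule and a general sentence that do not agree. The general sentence cannot settle the matter, since it refers to Table 4 for timing. A single misplaced tick is also not the obvious explanation, because the event screener, SDS and b-IPF share the pattern.

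A second reply concerns size. Veterans come partly by clinician referral and self-referral, so the screened mean could lie well above 10 and the bias would be small. At mean 20, SD 5 and r = 0.85 it is 0.04 points. This stands: the direction is fixed, the size is not.

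Third, a reader might infer that the standardised change is certainly inflated by a truncated SD. Table 3 does not name the standardiser, so this is conditional.

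Fourth, a reader might infer that a biased SDS could wrongly trigger the randomised trial. The Discussion ties that step to the primary outcomes, which are feasibility and acceptability, and nowhere says that the SDS will size the next trial.

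Finally, it is tempting to add that screening preceded the group by a long and variable wait. Table 2 puts recruitment and screening in the quarter before treatment, but no interval is stated. Screening and Baseline could even share an appointment, in which case a second SDS that day would help little.

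**Conclusion.** The point holds in conditional form. Table 4 and the study-measures section disagree on whether the lead exploratory clinical outcome has a Baseline measurement. If Table 4 governs, the starting SDS is the selection score and the uncontrolled change leans towards improvement. With a screened mean of 12 to 18, SD 7 and r = 0.7, the lean is about 0.5 to 1.3 points. Over r = 0.5 to 0.8 it is about 0.3 to 2.2 points. These values rest on assumed distributions, because the article gives none. The added inflation of a standardised change, by a factor of about 1.2 to 1.5, applies only if the pre-treatment SD is the divisor. The b-IPF is also used for selection and has the same gap in Table 4.

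Severity is moderate. The outcome is exploratory, is not formally tested, involves about 12 people, and does not govern progression. If a separate baseline SDS is in fact taken and used, the problem largely disappears.

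**What to change.** 1. Reconcile Table 4 with the study-measures section. Schedule the SDS and b-IPF at a Baseline assessment separate from screening, and define change as follow-up minus that score, never minus the screening score.
2. Recruitment for Aim 3 ended in January 2025, so some or all participants may have only a screening SDS. For them, keep the SDS as the declared lead exploratory outcome, since replacing it after enrolment would raise its own questions. Report the raw change with a plain statement about regression to the mean and a sensitivity range, for example r = 0.5 to 0.8, with the assumed screened mean and SD stated.
3. Name the standardiser, and do not use the SD of the screening scores.
4. Do not carry the uncorrected SDS change forward as an effect size for the later trial.

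The cost is one short repeat questionnaire where a Baseline assessment is still possible. Otherwise it is a few sentences of analysis wording and a slightly less favourable SDS figure.
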